We randomized these into 50 treatment clusters (containing 146 treatment villages) and 71 control clusters (containing 187 control villages). Six villages were randomly dropped to ensure UNICEF target numbers were met, while maintaining treatment and control balance.^[[3]](#footnote-3)^ We stratified randomization to ensure that the treatment and control groups are balanced with respect to their (i) province and (ii) number of villages that make up a cluster. Stratified randomization ensures that the treatment and control groups will be statistically indistinguishable from each other with respect to these characteristics, thereby avoiding bias in treatment effect.

Treatment clusters of villages will receive the status quo VEA intervention, as described above. Control clusters of villages will not receive any intervention from VEA. Data collection procedures will be identical in the two groups, as described below.

Additional discussions were held regarding the possibility of overlaying the school intervention as part of the impact evaluation. Due to the fact that the schools had been pre-selected in each province, this was not possible. There is, however, some possibility that the school intervention is differentially implemented in proximity to treatment and control villages which could threaten the validity of the results, particularly on schooling-related outcomes.

The IE team will work closely with UNICEF and local implementing partners to ensure accurate GPS and implementation tracking information is included in the planned data collection exercises to ensure that, if imbalance in proximity to treatment schools does occur, we will be able to adequately control for this in the analysis.

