# **Subgroup And Spillover analysis**

1. As with many interventions of this kind, it is likely that the VEA program may work differently for different socioeconomic groups. For instance, the program may have relatively larger effects on poorer/vulnerable communities, as compared to communities that are relatively affluent, and it may have larger effects on women than on men. Thus, in addition to estimating the main treatment effects, we will investigate potential heterogeneity of the VEA program based on several pre-treatment (or time-invariant) characteristics related to the VEA program or the local context. Our primary interest for sub-group analysis is to explore gender differences in time collecting water. We have additional exploratory interest in:
2. Province (each of the four provinces).
3. Distance to territory capital (a binary indicator for above or below the median distance for the province).
4. Education (a binary indicator for above or below median formal education of the household head).
5. Conflict history (a binary indicator for above or below the median number of conflict events experienced in a village prior to program onset).

Each subgroup analysis will cover the set of primary outcomes described in Section 4.

We model heterogeneous treatment effects by the following equation:

$y_{ihvc}= \alpha_{s}+\beta_{1}T_{c}+\beta_{2}T_{c}* Z_{c} + {\beta_{3}Z}_{c}+ \varepsilon_{i}$ (2)

where $y_{ihvc}$ is the outcome of interest for respondent *i* in household *h* in village *v* in cluster *c.* at the follow-up survey, defined above. $T_{i}$ is the treatment indicator that takes value 1 for clusters that were randomly assigned to participate in VEA (“treatment clusters”) and 0 for otherwise (“control clusters”). $Z_{c}$ is a vector of baseline characteristics (e.g. gender) by which we are interested in heterogeneous treatment effects. $\beta_{2}T_{c}* Z_{c}$ represents an interaction between the treatment and those characteristics. $\alpha_{s}$ captures stratum-specific fixed effects, where strata are based on province and number of villages in the cluster. $\varepsilon_{i}$ is an idiosyncratic error term. Our main parameter of interest is $\beta_{2}$.

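### Three exploratory effect modifiers are cut at the median before the interaction test, which loses information if the effect follows a gradient; test them on the full scale and keep the split as a companion

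*Protocol*

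**What the plan says.** The Protocol, under Subgroup And Spillover analysis, names one main subgroup question: "Our primary interest for sub-group analysis is to explore gender differences in time collecting water". It then adds a second tier, introduced by "We have additional exploratory interest in", with four items. Province is categorical by nature. The other three are dichotomised:

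- "Distance to territory capital (a binary indicator for above or below the median distance for the province"
- "Education (a binary indicator for above or below median formal education of the household head"
- "Conflict history (a binary indicator for above or below the median number of conflict events experienced in a village prior to program onset"

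Each enters equation (2) as Z. The product of treatment and Z "represents an interaction between the treatment and those characteristics", and its coefficient, beta2, is the one referred to by "Our main parameter of interest is". The section gives no reason for the cuts, plans no analysis on the uncut scale, and does not say where a value exactly at the median belongs.

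**The concern.** Distance is continuous, conflict events are a count, and education is at least ordered. Cutting at the median treats two villages just either side of it as opposites, and two villages far apart on the same side as identical. Equation (2) would accept an uncut Z without change. The section argues that effects may be larger in poorer or more vulnerable communities. It names no threshold, and nothing suggests a jump at the sample median.

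With 121 randomised clusters and a planning intra-cluster correlation of 0.7, interaction tests on village-level modifiers have little precision to spare. At stake is a real gradient, for example by remoteness or conflict exposure, being reported as no heterogeneity although the graded data are in hand.

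**Working it through.** **Inputs from the Protocol.** Allocation: "We randomized these into 50 treatment clusters (containing 146 treatment villages) and 71 control clusters (containing 187 control villages", so 121 clusters and 146 + 187 = 333 villages. Four households per village, planning intra-cluster correlation 0.7, alpha 5% and power 80% (Sample size and power calculations). Sidedness is not stated; two-sided is used here.

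**Inputs assumed.** The distribution of each modifier and the size of any interaction; the Protocol gives neither. Its only detectable-effect figure is for the main effect on improved water, so there is no interaction figure to reproduce.

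**1. Information kept.** If the effect is linear in Z, replacing Z by a split S multiplies the information on beta2 by corr(Z, S)².

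- Normal Z: corr = √(2/π) = 0.798, squared 0.637, so 36.3% is lost.
- Uniform Z: corr = √3/2 = 0.866, squared 0.75, so 25% is lost.

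**2. Power.** For a full-scale test with 80% power the noncentrality is 1.960 + 0.842 = 2.802.

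- Normal: Φ(2.802 × 0.798 − 1.960) = 61%.
- Uniform: Φ(2.802 × 0.866 − 1.960) = 68%.

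In the normal case the loss equals using 121 × 0.637 = 77 clusters, and the detectable interaction is 1/0.798 = 1.25 times larger.

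**3. Other assumed shapes** (1,000,000 draws each). Where two values are shown, the first puts ties below the cut and the second above it.

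| Shape of Z | Kept | Lost |
|---|---|---|
| Two-peaked mixture | 0.813 | 19% |
| Poisson, mean 1 | 0.696 / 0.582 | 30% / 42% |
| Poisson, mean 3 | 0.660 / 0.617 | 34% / 38% |
| Gamma, shape 2 | 0.553 | 45% |
| Lognormal, log-SD 0.5 | 0.517 | 48% |
| Exponential | 0.480 | 52% |
| Negative binomial, mean 1, k 0.3 | 0.419 / unusable | 58% |
| Negative binomial, mean 3, k 0.5 | 0.408 / 0.261 | 59% / 74% |
| Lognormal, log-SD 1 | 0.271 | 73% |

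The larger losses assume an effect linear in the raw, skewed value. If the effect is instead linear in the log of a lognormal modifier, the log is normal and the loss returns to 36%.

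**4. Which test wins depends on the truth.** A simulation of 121 cluster-level values (50/71, normal Z, 4,000 runs) gave:

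| True effect | Full scale | Split |
|---|---|---|
| Linear in Z | 78% | 58% |
| Step at the median | 58% | 79% |

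**5. A run closer to the design.** 121 clusters, 333 villages, 4 households each, correlation 0.7, province dummies, cluster-robust errors, 800 runs, village-level Z, interaction 0.4 SD per SD of Z.

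| Z | Power, split | Power, full scale | Null rejection, split | Null rejection, full scale |
|---|---|---|---|---|
| Normal | 60.5% | 75.9% | 6.0% | 6.9% |
| Uniform | 69.0% | 74.5% | 5.6% | 6.3% |

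The Monte Carlo standard error of a power near 60% is √(0.6 × 0.4/800) = 1.7 points. For a household-level modifier such as education, with interaction 0.08, power was 23% (split) against 34% (normal) and 26% against 33% (uniform). With interaction 0.05 it was 12% against 17% and 14% against 16%.

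**6. Ties.** For a Poisson count with mean 1, 26% lie above the median and 63% at or above it. For the negative binomial with mean 1 and k 0.3 the median is 0, so only a strictly-above cut forms two groups (36% above).

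**The case against.** The strongest reply is that this is largely a matter of preference in analyses the plan itself calls exploratory. A pre-specified split is easy to report, assumes no scale or linearity, and limits later choice of functional form. It also resists gross errors in the modifier, which is relevant because a footnote to the Randomization Annex admits that some GPS points are plainly wrong. For education the gain is small in absolute terms, since power is low either way.

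Much of this stands, and it limits the weight of the point. It does not remove it. The split's advantages can be kept by retaining it beside the full-scale test, and the functional form can be fixed in advance just as firmly. The higher null rejection of the full-scale test for a normal modifier (0.9 points) cannot account for a power gap of 15.4 points.

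Two stronger readings are tempting. A reader might infer that the plan throws away a third of the information on all three modifiers. That figure needs a normal modifier and a linear gradient, and the Protocol supplies neither. A reader might also take the contrast for a right-skewed modifier in the same simulation (44% split, 79% full scale) as the expected gain. That comparison enters the raw value, which is not what is recommended, and the raw-scale test rejected 8% under the null against 5% for the split.

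The simulation also simplifies: it uses province dummies rather than the full strata, and a continuous outcome although two of the four primary outcomes are binary.

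**Conclusion.** The plan fixes a coding for three exploratory modifiers that costs precision whenever the effect follows a gradient, and gives no reason for it. Under a linear gradient the loss is 36% for a normal modifier, 25% for a uniform one and 19% to 74% over all shapes tried; it is zero if the effect steps at the median. These are conditional figures: the distributions and interaction sizes are assumed.

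A reader might infer that the trial's main conclusions are weakened. The Protocol does not support that: the intention-to-treat estimates, the false-discovery-rate adjustment of the four primary outcomes and the gender subgroup do not use these cuts. This is a cheap improvement, not a necessary correction.

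**What to change.** In the list under Subgroup And Spillover analysis, state that beta2 of equation (2) is tested with each modifier on its full scale:

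- distance to territory capital: log distance, centred within province, which keeps the within-province comparison of the present definition;
- education of the household head: years, or ordered level if years are not recorded;
- conflict history: log(1 + number of events).

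Keep the pre-specified median split as a companion analysis displayed by group, and state on which side values equal to the median fall. Leave the province modifier and the gender analysis as they are.

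The cost is the wording of three list items and a few more model runs, with no new data. The downside is that the full-scale test assumes a roughly linear gradient on the chosen scale (equal spacing, if ordered education levels are used), is weaker if the effect steps at the median, and is more sensitive to gross errors in the modifier. The retained split covers those cases.

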# **Appendix**: Randomization Annex

UNICEF provided DIME with a set of 403 georeferenced villages across the 5 districts of Kongo Central, Kasai, Kasai Central, South Kivu and North Kivu, where villages were defined based on the EVA program definition. From this dataset, 34 villages from Kasai Central were already indicated to have been assigned to receive the program, leaving a universe of 369 program villages to conduct the randomization. The main requirements that were imposed on the randomization were:

1. The number of treatment villages needed to match exactly with the number of UNICEF target villages for the program in each province.
2. Due to concerns of possible spillovers, the randomization needed to cluster villages deemed to be too close to each other.

*What were the clustering rules used?* In rural provinces (Kasai, Kasai Central and Kongo Central) any village within 2.5km (as the crow flies) of another village would be considered as part of the same cluster. This was discussed as an appropriate distance to avoid meaningful spillovers since it would imply an approximately 45-minutes one-way journey to the program water source on average which far exceeds the SDG definition of improved water requiring that a round trip take 30 minutes or less. The more densely populated urban areas (South and North Kivu) require a modified clustering rule to avoid all villages joining a single cluster. Here the procedure is to cluster all program villages that belong to the same administrative villages into single clusters (i.e. consider the administrative village rather than the program village as the unit of randomization). However, some administrative villages lie very close to one another. As an additional level of clustering, we then combine all administrative villages that lie within 1km of each other^[[5]](#footnote-5)^.

Once clusters are identified, we randomize clusters into treatment and control groups, stratifying by province and cluster size to ensure balance. In all provinces except Kasai Central, each cluster is given equal probability of being selected for treatment or control. In Kasai Central, we increase the probability of being selected into the control group proportionally to reflect the fact that only 16 out of 81 villages from the sampling frame were required to be assigned to receive treatment.

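### Subgroup model (2) gives the subgroup variable one slope for all provinces although the treated share is about 0.2 in Kasai Central and 0.5 elsewhere, so β2 can pick up a province difference in the untreated gradient

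*Protocol*

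**What the plan says.** Under Subgroup And Spillover analysis, equation (2) regresses the outcome on a stratum intercept α_s, treatment T (coefficient β1), the product T×Z (β2) and Z (β3). The intercept "captures stratum-specific fixed effects, where strata are based on province and number of villages in the cluster". The product term "represents an interaction between the treatment and those characteristics", and β2 is named as the parameter of interest for this model. There is one β3 for the whole sample. No Z-by-stratum term and no weighting is mentioned.

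The leading subgroup question is gender: "Our primary interest for sub-group analysis is to explore gender differences in time collecting water". Province, distance to the territory capital, education of the household head and conflict history are listed as exploratory.

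The Appendix (Randomization Annex) describes unequal allocation: "In all provinces except Kasai Central, each cluster is given equal probability of being selected for treatment or control". By contrast, "In Kasai Central, we increase the probability of being selected into the control group proportionally", because "only 16 out of 81 villages from the sampling frame were required to be assigned to receive treatment".

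**The concern.** Treatment is independent of Z only within strata, and the assignment probability differs between strata. The intercepts α_s take care of this for the main effect. They do not do so for the interaction, because T×Z is correlated with Z-by-province, which equation (2) leaves out.

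Put simply, the treated and the control villages average the Z gradient over different mixes of provinces. If households with more educated heads have, say, a larger untreated advantage in Kasai Central than elsewhere, the control arm shows a steeper average education gradient than the treated arm, and β2 reads that gap as effect modification. A real interaction could be hidden in the same way. Clustered standard errors do not address this, and the larger endline sample foreseen in the Introduction would not remove it.

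**Working it through.** **Inputs.** Village counts come from the table in the Randomization Annex. With 4 households per village (Sample size and power calculations), household shares equal village shares.

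| Province | Treated | Control | Treated share | % of treated arm | % of control arm | Difference |
|---|---|---|---|---|---|---|
| Kongo Central | 20 | 18 | 0.526 | 13.7 | 9.6 | +0.041 |
| Kasai | 50 | 44 | 0.532 | 34.2 | 23.5 | +0.107 |
| Kasai Central | 16 | 65 | 0.198 | 11.0 | 34.8 | -0.238 |
| South Kivu | 60 | 60 | 0.500 | 41.1 | 32.1 | +0.090 |
| Total | 146 | 187 | | 100 | 100 | 0 |

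The totals reproduce the Protocol's 146 and 187. Outside Kasai Central the treated share is 130/252 = 0.516. By cluster the contrast is 8/37 = 0.216 against 42/84 = 0.500.

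**Formula.** Let g_s be the untreated gradient of the outcome on Z in province s. Assume a constant treatment effect, no true interaction, and the same prevalence of Z in every province. Least squares on equation (2) then sets β3 to the control arm's average gradient and β3 + β2 to the treated arm's average gradient, so

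bias(β2) = Σ (treated-arm share - control-arm share) × g_s = 0.041 g(Kongo Central) + 0.107 g(Kasai) - 0.238 g(Kasai Central) + 0.090 g(South Kivu).

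This equals -0.238 × [g(Kasai Central) - ḡ], where ḡ = 0.171 g(Kongo Central) + 0.450 g(Kasai) + 0.379 g(South Kivu). The weights are 0.041, 0.107 and 0.090, each divided by 0.238 (unrounded). Writing d for the bracket, the bias is -0.238d. With cluster counts as weights it is -0.248d. In the cases tried with unequal prevalence of Z it was between -0.21d and -0.22d. It is zero if the gradients, or the allocation shares, are equal in all provinces.

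Province intercepts stand in for the strata here, because the annex describes allocation as varying by province and does not list the cluster-size strata.

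**Size under assumed d** (not given in the Protocol):
- d = 10 points: -0.238 × 10 = -2.4 points
- d = 20 points: -4.8 points
- d = 30 points: -7.1 points
- Gender, if the female-male gap in collection time is 30 minutes larger in Kasai Central: -7.1 minutes

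**False positives.** These come from a simulation with the Protocol's cluster and village counts, control level 0.42, intra-cluster correlation 0.7, no true interaction, nominal 5% and 600 runs per case. For household-level Z, rejection was about 7% at d = 0 and 7%, 11% and 21% at d = 10, 20 and 30 points. For village-level Z it was about 6%, 7% and 11% at d = 10, 20 and 30. A separate run for village-level Z (500 runs, continuous outcome with SD 0.49) gave 6.2%, 7.2%, 8.8% and 12.2% at d = 0, 10, 20 and 30.

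**Remedies, by exact solution over province × T × Z cells:**
- Constant treatment effect, gradient differing in Kasai Central: Z-by-province slopes bring the bias to 0, and so does inverse-probability weighting.
- Treatment effect differing by province. Assumed effects are 10, 20, 20 and 40 points and prevalence of Z 30, 40, 50 and 80% in Kongo Central, Kasai, Kasai Central and South Kivu, with no gradient difference and no within-province interaction. β2 is +0.083 under equation (2), +0.090 with Z-by-province slopes alone, +0.083 with weighting alone, and 0 with both Z-by-province and treatment-by-province terms.
- The same province effects with equal prevalence of Z: β2 is 0 under all of these models.

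**The case against.** The strongest reply concerns reach and size. Apart from gender, the subgroups are declared exploratory, and the trial's main parameter is β1 in equation (1), which has no T×Z term. The value of d is wholly assumed. At d = 10 points the simulated rejection rates cannot be told apart from those with no gradient difference. For village-level Z (distance and conflict history) the SD of β2 is about 0.095, so a 5-point bias is about half a standard error, in an analysis that could detect only interactions of about 2.8 × 0.095 = 0.27. The higher error rates need a household-level Z and d of 20 to 30 points. For improved water that is hard to reach, since the Protocol expects households in a village to share sources and treats 42% as an upper bound for the control level.

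All of this stands and limits the severity. It does not remove the defect: the equation is written out in full, β2 is its stated target, and its leading application is gender differences in collection time, where these arguments about shared sources do not apply. With no baseline survey, the gradients could not be checked in advance.

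A reader might infer that any provincial difference in gradient biases β2. It does not: the bias cancels when Kasai Central's gradient equals the weighted mean of the other three, and differences among the three provinces with near-equal allocation matter less. A reader might also take inverse-probability weighting as equivalent to adding slopes, or take either as a complete cure. Weighting is a different estimator, and neither removes the second bias shown above.

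**Conclusion.** The point holds for the subgroup models. With the Protocol's own allocation, equation (2) gives a β2 that is off by about -0.24d when there is no true interaction, where d is the excess of Kasai Central's untreated gradient over the weighted mean of the others. The coefficient follows from the allocation table, assuming similar prevalence of Z across provinces; d is unknown. At assumed d of 10, 20 and 30 points the bias is about -2, -5 and -7 points. The effect on error rates is slight at the low end and for village-level Z, and material for household-level Z at the high end.

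The documents do not support reading this as a flaw in the trial's main result. Equation (1) is not affected, nor is the province subgroup, where α_s already absorbs the main effect of Z. This is a correction worth making to a pre-specified model, not a threat to the primary conclusions.

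**What to change.** In equation (2), replace β3·Z with province-specific slopes (Z interacted with the four province dummies), keeping α_s and a common β2. Apply this to the gender (collection time), distance, education and conflict-history subgroups.

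Where the prevalence of Z can differ by province, also add treatment-by-province terms. This concerns education and conflict history, whose medians, unlike that for distance, are not stated to be taken within province. Otherwise province differences in the treatment effect load onto β2. If inverse-probability weighting is preferred, state that it deals with the gradient bias only.

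The cost is three extra coefficients per model for the slopes, three more where treatment-by-province terms are used, and no new data. In the simulation the slopes left the SD of β2 almost unchanged: 0.053-0.057 against 0.052-0.056 for household-level Z, and 0.095-0.101 against 0.091-0.098 for village-level Z. The precision cost of the treatment-by-province terms was not simulated; some further loss should be expected.

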# **Study Design**

## Treatment and Control Groups

Our goal is to estimate the causal effects of the core VEA program with a randomized control trial. The unit of treatment is the village; thus, a straightforward randomization would be at the village level. However, VEA villages can be quite close to one another, raising the possibility of spillover effects from treatment villages to control villages (e.g. people in control villages accessing new water points in treatment villages). Therefore, we grouped villages into clusters. We considered any villages within 2.5 km of each other (with distance determined “as-the-crow-flies”) to be part of the same cluster. Therefore, all clusters have at least 2.5 km between them. We relax this rule in South Kivu, where density is greater and we seek to include naturally occurring villages, rather than the smaller unit of VEA sub-villages, in the sample. In cases where naturally occurring/administrative villages are less than 1 km from each other, we aggregate these into a single village cluster.

UNICEF generated and shared with the research team a list of 403 candidate villages based on the established criteria for the program: the village is located in a secure and accessible Health Area that is not already served by the WASH Consortium, the Health Area staff are dynamic and interested in participating, and there is a problem of diarrhea, cholera, and/or malnutrition.^[[2]](#footnote-2)^ Thirty-four of these villages were already in process (in Kasai Central), leaving 369 eligible villages in five provinces: Kongo Central, Kasai, Kasai Central, South Kivu, and North Kivu. Based on the rules above, we grouped those villages into 124 clusters. North Kivu had only three clusters (covering 30 villages), so we decided that it was not logistically efficient to work there. That left us with 121 clusters in four provinces and 339 villages.

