In South Kivu, some treated clusters may be just over 1 km from control clusters. To probe for potential spillovers, we follow Null *et al*. (2018) and test whether primary outcomes were the same in control households with more versus fewer households receiving interventions within a 2 km radius.^[[4]](#footnote-4)^ This will allow us to assess whether spillovers may be a concern for the primary analysis where we focus on direct effects.

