Since randomization is based on clusters but UNICEF targets are based on villages, it is not possible to force the randomization to select the exact number of UNICEF villages targeted without introducing potential bias. Instead we compare the number of UNICEF target villages per province to the number of treatment villages selected after randomization. In cases where the number of treatment villages is larger than the target, we randomly drop an equal number of program villages from the largest control and treatment clusters until targets are met. For Kongo Central this meant dropping 2 villages and for Kasai this meant dropping 4 villages split equally from the largest treatment and control clusters.

The result of the randomization selection is summarized in the below table:

| **Province** | **Total sampling frame of villages received** | **Treatment villages (clusters)** | **Control villages (clusters)** | **Villages dropped** |
| --- | --- | --- | --- | --- |
| **Kongo Central** | 40 | 20 (9) | 18 (9) | 2 |
| **Kasai** | 98 | 50 (20) | 44 (19) | 4 |
| **Kasai Central** | 81 | 16 (8) | 65 (29) | 0 |
| **South Kivu** | 120 | 60 (13) | 60 (14) | 0 |
| **Total** | **339** | **146 (50)** | **187 (71)** | **6** |
| ***North Kivu*** | *Excluded due to lack of clusters (3) from the province* | | | |

1. Arguably, the proposed mechanisms or channels cannot be identified causally within the current study design. Rather, these will be investigated through qualitative research. [↑](#footnote-ref-1)
2. Unicef. Logigramme Villages et Ecoles Assainis. Guide de Sélection des Villages et des Ecoles. Version février 2014. Fichier .ppt. [↑](#footnote-ref-2)
3. A more detailed description of the sampling and randomization can be found in the Randomization Annex. [↑](#footnote-ref-3)
4. We note that this is a robustness check rather than a formal test to try find spillovers. [↑](#footnote-ref-4)
5. In practice, we find the centroid of all GPS points of program villages that are clustered into an administrative unit and compare this centroid between clusters to assess how close each administrative village is. In some cases, GPS points are clearly inaccurate (e.g. indicating that a program village lies in the water). In these cases, we remove that village GPS from the centroid calculations and rely on the other program villages that are part of the same cluster. [↑](#footnote-ref-5)

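### The 2 km spillover check has almost no designed exposure outside South Kivu, and the plan neither limits it to that province nor adjusts for strata or local village density

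*Protocol*

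**What the plan says.** The section on treatment and control groups sets the general separation rule, under which "all clusters have at least 2.5 km between them", and then makes one exception: "We relax this rule in South Kivu, where density is greater". The Randomization Annex names the provinces under the general rule: "In rural provinces (Kasai, Kasai Central and Kongo Central) any village within 2.5km (as the crow flies) of another village" joins that village's cluster. For South Kivu, programme villages are first grouped by administrative village, and "we then combine all administrative villages that lie within 1km of each other".

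The spillover paragraph at the end of the subgroup section opens with the reason for the check: "some treated clusters may be just over 1 km from control clusters". It then follows a cited study and tests whether primary outcomes are equal in "control households with more versus fewer households receiving interventions within a 2 km radius". It says the result will help assess whether spillover is a concern for the primary analysis. Footnote 4 describes this as a robustness check and not a formal test.

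The paragraph gives no province limit on the control households, no model, no strata terms and no cut-off between high and low exposure. Equations (1) and (2), by contrast, both carry stratum effects based on province and number of villages in the cluster.

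**The concern.** The exposure radius (2 km) is shorter than the minimum separation (2.5 km) in three of the four provinces. Controls there have essentially no designed variation in exposure to randomised treatment villages, so any comparison of high with low exposure draws its high group from South Kivu. The sentence refers to control households in general. If it is applied to all of them without province terms, an ordinary difference between South Kivu and the other provinces could be reported as spillover, or could mask it.

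A second problem remains inside South Kivu. A control household in a dense area has more treated households nearby simply because it has more study villages of both kinds nearby. Density may itself be related to water sources, collection time and sanitation. Treatment assignment is random, but the raw number of treated neighbours is not.

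South Kivu has 120 of the 333 randomised villages in the Annex table (36%), the most of any province. At the Annex's own pace (2.5 km in about 45 minutes), 1 km is 45/2.5 = 18 minutes one way, so use of a neighbouring cluster's water point is plausible there. A misleading check would leave that question open where it matters most.

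**Working it through.** **Inputs** (Annex table, villages with clusters in brackets)

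| Province | Treatment | Control | Separation rule |
|---|---|---|---|
| Kongo Central | 20 (9) | 18 (9) | 2.5 km |
| Kasai | 50 (20) | 44 (19) | 2.5 km |
| Kasai Central | 16 (8) | 65 (29) | 2.5 km |
| South Kivu | 60 (13) | 60 (14) | 1 km |

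**Step 1. Reproduce the table totals.** Treatment: 20+50+16+60 = 146 villages and 9+20+8+13 = 50 clusters. Control: 18+44+65+60 = 187 villages and 9+19+29+14 = 71 clusters. Both agree with the Protocol.

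**Step 2. Controls with no randomised treatment village in range.** Since 2 < 2.5, these are the controls outside South Kivu, by village location.
- Clusters: 9+19+29 = 57 of 71 (80%).
- Villages: 18+44+65 = 127 of 187 (68%).
- Households, at 4 per village: 508 of 748.

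What remains is 14 clusters, 60 villages and about 240 households, all in South Kivu. With 68% of controls at zero, a median split over all controls would cut at zero.

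**Step 3. Make-up of a pooled, unadjusted comparison.** Let f be the share of South Kivu control villages with any treated village within 2 km. The Protocol gives no exposure counts, so f is varied. The share of the low-exposure group from the other provinces is 127/(187 − 60f).

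| f | Share from other provinces |
|---|---|
| 0.10 | 127/181 = 70% |
| 0.25 | 127/172 = 74% |
| 0.50 | 127/157 = 81% |
| 1.00 | 127/127 = 100% |

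The high-exposure group is all South Kivu, so the same fraction (0.70 to 1.00) of any gap between South Kivu and the other provinces enters the contrast.

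**Step 4. Simulation with no spillover.** Assumptions: a 20-percentage-point gap between South Kivu and the rest, outcome SD 0.45, the plan's intra-cluster correlation of 0.7, analysis of cluster means, and 30%, 50% or 70% of the 14 South Kivu clusters exposed at random (4, 7 or 10 clusters); 1,500 repetitions each.

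| Exposed | Pooled: mean contrast, rejection at 5% | Province effects | South Kivu only |
|---|---|---|---|
| 30% | 0.173, 12.9% | 0.004, 4.9% | 0.004, 4.8% |
| 50% | 0.174, 20.3% | −0.005, 5.1% | −0.005, 5.5% |
| 70% | 0.180, 27.2% | −0.008, 4.0% | −0.008, 4.5% |

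Direct arithmetic at cluster level agrees. With 7 exposed clusters, 57 of the 64 unexposed clusters lie elsewhere, and 57/64 × 0.20 = 0.178.

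**Step 5. Density within South Kivu.** Exposure in step 4 was random within the province, so the simulation does not test this part. For a control cluster, 13 of the other 26 South Kivu clusters are treated, so the expected number of treated clusters in range is about 13/26 = 0.5 times the number in range. Two clusters in range give about 1 treated, and six give about 3 (illustrative counts). Expected exposure is thus proportional to local density. The strata use the number of villages in the household's own cluster, not the number in neighbouring clusters, so stratum dummies leave this in place. Conditioning on the total in range removes it, because what then varies is which neighbours drew treatment.

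**The case against.** The strongest reply is that the paragraph opens with South Kivu, where a 2 km radius suits a 1 km rule, so the check may be meant for that province alone. A reader might infer that the plan prescribes a pooled, unadjusted test. It does not say so. Both stated models carry province-based strata, and if these carry over, step 4 shows the province distortion disappears. The model for a secondary check can also be left to an analysis plan that is not shown, and the cited method may handle density in ways the Protocol does not repeat. All of this stands, and it limits the point to an open scope and an incompletely specified contrast. But the radius and the exposure contrast are fixed in this document, and their mismatch with the separation rule is visible here.

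Other tempting readings go too far:
- **That the check compares provinces instead of testing spillover.** Even pooled, South Kivu controls with differing exposure contribute some within-province information, unless all are exposed.
- **That exposure is zero for everyone elsewhere.** The count above concerns randomised villages at their mapped locations. The 34 Kasai Central villages already in process were removed before clustering and could lie within 2 km of controls. Kasai Central supplies 29 of the 57 clusters and 65 of the 127 villages. Exposure to those 34 was not randomised in this trial.
- **That the centroid rule undermines the check.** Footnote 5 says "we find the centroid of all GPS points of program villages that are clustered into an administrative unit", but this governs how clusters were formed. The exposure radius is drawn around control households, and the 1 km distance is described only as something that may occur.
- **That spillover must bias every primary effect toward zero.** This is plausible for improved-source use. For collection time, controls walking further to a treated point could widen the difference.

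Footnote 4's caveat also stands: no decision rule hangs on the check. The plan still intends to use it to judge whether spillover is a concern for the primary analysis, so it should be able to inform that judgement.

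**Conclusion.** The point holds as a gap in specification with a concrete remedy. By village location, 80% of control clusters and 68% of control villages have no randomised treatment village within 2 km, and the check rests essentially on 14 South Kivu control clusters. If it were run on all controls without strata terms, it would carry 0.70 to 1.00 of any gap between South Kivu and the other provinces. With an assumed 20-point gap and no spillover, it would show about 17 to 18 points and reject 13% to 27% of the time. Those figures depend on the assumed gap, SD and exposed share, none of which the Protocol gives. The documents do not establish that the pooled, unadjusted version is what will be run.

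Restricting to South Kivu or adding stratum effects resolves the province problem. It does not resolve confounding with local density, whose size cannot be computed without the village locations. Whatever the model, the check is essentially uninformative about spillover between randomised clusters in Kongo Central, Kasai and Kasai Central. The primary estimate is not itself affected; what suffers is the reassurance offered about it.

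**What to change.** Replace the spillover sentence with a short specification:

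1. Limit the check to South Kivu control households, or include the province and stratum effects of equation (1).
2. Regress each primary outcome on the number of treated study villages (or households) within 2 km, conditional on the total number of study villages (or households) of both arms within 2 km. Cluster standard errors by village cluster. If a split into high and low exposure is kept, define the cut-off.
3. Report the estimate with its confidence interval.
4. Say whether the 34 in-process Kasai Central villages count as exposure.
5. State that the check is essentially uninformative about spillover between randomised clusters in the other three provinces.

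The cost is one paragraph and a small regression. The candidate villages were supplied georeferenced, and the plan already commits to GPS tracking. The downside is precision: with 14 control clusters the interval will be wide, and it should be presented as such.
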